### Pain Worrying (Pain Catastrophizing): Pain Catastrophizing Scale

This scale [142] contains 13 items that are rated on a 5-point scale ranging from 0=*not at all* to 4=*all the time*. It assesses the 3 components of catastrophizing: rumination, magnification, and helplessness. The total score ranges from 0 to 52 points. Higher scores reflect higher levels of catastrophic thoughts. The Spanish version [143] presents strong psychometric properties.

### Pain-Related Self-Efficacy: CP Self-Efficacy Scale

This specific scale [144] for patients with CP helps measure perceived self-efficacy and capability to manage pain consequences. It is composed of 22 items structured across 3 factors: self-efficacy to control pain, self-efficacy for physical functioning, and self-efficacy for symptom control. It is a well-known instrument that has been validated with the Spanish population with good psychometric properties [145]. In the Spanish version items are rated from 0=*I think I am totally incapable* to 10=*I think I am totally capable*, with a higher score suggesting higher self-efficacy in a specific factor or in the overall measure of self-efficacy.

### Informal Social Support: Informal Social Support for Autonomy and Dependence in Pain Inventory

This instrument [146] consists of 11 items designed to measure both emotional and instrumental social support in relation to promoting functional autonomy or addressing functional dependence. Participants are asked to rate how frequently their family members have provided support when they were in pain. In our case we specifically ask on the support they receive from their intimate partners. Only women currently in a relationship will be required to complete this section. Responses are provided on a Likert scale ranging from 1=*not at all frequent* to 5=*extremely frequent*. Higher scores indicate that participants perceive more frequent support for functional autonomy or dependence. This instrument has demonstrated validity and reliability in its original form and has been validated with the Spanish population [146].

#### Variables and Instruments for Health Outcomes

### Health-Related Quality of Life: Short-Form Health Survey-12

This tool [147] consists of 12 items that measure both positive and negative health states across 8 health concepts (physical functioning, role limitations because of physical health problems, bodily pain, general health, vitality, social functioning, role limitations because of emotional problems, and mental health). It offers 2 physical and mental health summary measures. The responses are based on Likert scales ranging from 3 to 5 points. This questionnaire has been validated for use with the Spanish population [148].

### Physical Functioning: Brief Pain Inventory–Short Form

The Brief Pain Inventory–Short Form [149] assesses pain severity and pain interference. The latter includes 7 items that assess pain’s impact on various areas of life (general activity, mood, ability to walk, work, social relationships, sleep, and the ability to enjoy activities), which participants rate on a 10-point scale (maximum score=70). For the purpose of evaluating physical functioning, items related to general activity, ability to walk, and ability to work will be selected, with a maximum score of 30. This instrument has been validated for use with the Spanish population [150].

### Anxiety and Depression: Hospital Anxiety and Depression Scale

This scale [151] includes 2 subscales, one for anxiety and one for depression, each with 7 items and a 4-point response scale ranging from 0=*no presence or minimum presence* to 3=*maximum presence*. The scale assesses emotional distress in patients with chronic conditions, focusing on the cognitive and behavioral symptoms of anxiety and depression. The recommended cutoff scores for possible cases are 8 for both subscales, with scores of >10 indicating probable cases. This scale has been widely validated across multiple countries, including Spain, and demonstrates strong psychometric properties [152].

### Suicide Attempts and Thoughts: Ad Hoc Questionnaire

Participants will be asked whether they have ever considered committing suicide (yes or no); how frequently they have had such thoughts (never, rarely, sometimes, often, or always); and the number of suicide attempts, if any.

### Medication Use and Illegal Drug Use: Ad Hoc Questionnaire

Participants will be asked to indicate the types of analgesics prescribed for their CP condition and their adherence to the prescribed medication regimen. They will be asked if they are taking the medication as prescribed, not taking it at all, or taking it in lesser or greater amounts. The questionnaire will also inquire about the use of nonprescribed medications and the consumption of other legal (eg, alcohol) and illegal drugs (eg, marijuana) for pain management. In addition, participants will be asked about other prescribed medications they may be taking and the purposes for which these medications are used.

### Health Service Use: Ad Hoc Questionnaire

Participants will be asked about the frequency of visits to their general practitioner. Specifically, they will be asked how many times per month they visit their general practitioner, with the following response options: none, only when needing medication prescriptions or check-ups, at least once a month, or ≥2 times per month.

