#### CP Outcomes

How individuals manage CP can have deep and long-lasting effects on their quality of life. Effective management can minimize pain, reduce physician visits, empower patients to participate in treatment decisions, and provide a sense of control over their lives [110-114]. By contrast, poor CP management can negatively impact socialization, reduce participation in social events, and decrease independence, leading to isolation [115,116]. It can also increase vulnerability to suicide and suicidal ideation [110] as well as contribute to the misuse of both licit and illicit drugs—such as alcohol, marijuana, or heroin—for pain relief [117-119], which, in turn, further strains health systems. Pain is one of the primary reasons for medical consultations worldwide, accounting for 22% of visits [120,121]. People with CP visit their general practitioner twice as often as those without CP [122], and they are more likely to use emergency services and unscheduled care [123,124]. In Spain, CP is the second most common reason for primary care consultations, with >50% of visits related to this condition [125].

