### Phase 1: Qualitative Study (General Aim 1, Specific Objectives 1 to 4)

#### Overview

We will use a qualitative approach with a descriptive and exploratory design, conducting individual semistructured interviews. Focus groups are not considered due to the necessity of maintaining the anonymity of those experiencing IPV against women. The results of this phase will allow us to incorporate any additional relevant factors or health outcomes into the study’s second phase.

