#### Sample Size Calculation

To calculate the sample size, the prevalence of the pain-avoidance activity pattern was used, which is typically present in cases of highly disabling CP [102]. Specifically, we considered several factors: first, the expected prevalence ratio assumed to be 2.0 between individuals with CP who are exposed to IPV against women and those who are not. Second, we estimated the prevalence of the pain-avoidance activity pattern within the study population, assuming it to be approximately 20%. While a previous study found that 40.4% of patients with fibromyalgia exhibited this pattern [133], we decided to use a more conservative estimate, given that the prevalence of this behavior is likely lower among the broader population of patients with CP. Finally, we accounted for the expected prevalence of IPV exposure among women with CP, estimated at 30% based on findings from earlier research [23].

We have defined the risk level α as 5% and the study power as 90%. The program used for size calculation was a macro, !NSize, for SPSS Statistics [134]. On the basis of these parameters, the required sample size consists of 359 women with CP: 193 (53.8%) with CP alone, 83 (23.1%) with CP and a current history of IPV, and 83 (23.1%) with CP and a past history of IPV.

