#### Data Analysis

Inferential statistics help researchers draw conclusions about populations based on sample data, providing insights into social phenomena [153]. Machine learning, as a subset of artificial intelligence (AI) techniques, analyzes large datasets to identify patterns and make predictions [154]. These methods are transformative in gender studies, uncovering patterns in gender-related data and deepening the understanding of social inequalities and biases [155]. These methods have been successfully applied to areas such as forecasting gender-based violence, further demonstrating their relevance in social sciences [156].

Exploratory data analysis (EDA) will be crucial in examining CP and its connection to past or current IPV against women. EDA uses techniques such as scatterplots, clustering algorithms, and principal component analysis to investigate multidimensional datasets [157]. Scatterplots help identify correlations between sociodemographic variables, clustering algorithms reveal subgroups within the population, and principal component analysis reduces dimensionality to uncover latent factors such as the relationship between gender identity and social support [158]. The use of EDA will allow us to detect groups and subgroups at a glance by creating subclusters, that is, more specific profiles in each of the groups.

Inferential statistical methods will be applied to differentiate between women with CP alone and those with CP who have experienced IPV in the past or are currently experiencing IPV. Hypothesis testing, estimation, and prediction techniques will be used to make comparisons, with visual tools such as boxplots for examining variable distributions across groups. We will use 2-tailed *t* tests and ANOVA to compare means across groups [159].

Feature ranking techniques will help identify the most relevant variables for accurate classification. Methods such as information gain, gain ratio, Gini index, and relief will determine the importance of features such as education, socioeconomic status, pain level, and social support [160]. This feature ranking will help prioritize the most influential factors affecting each group, including those based on country distribution.

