## Discussion

### Summary

This project has 2 main aims. The first is to acquire knowledge on the meaning and implications of living with CP for women experiencing IPV compared to those with CP alone. In this regard, we hypothesize that (1) women who experience any form of IPV (psychological, physical, or sexual) will report a greater daily impact of CP on their functionality than those with CP alone; (2) compared to the latter, the former will report a stronger bidirectional relationship between CP and intimate relationship dynamics as well as worse health outcomes (ie, episodes of violence will increase CP symptomatology and vice versa), with such a negative cycle being more prevalent; and (3) CP management and experiences with the health system will be better among women with CP alone. Hypotheses 1 and 3 are based on the fact that some authors have highlighted that the impact of IPV against women on the health of those affected adds to CP [31]. This could impair their ability to self-manage CP, leading to increased medication use and more frequent visits to health centers [165]. We believe that this result will be independent of the type of violence experienced because studies have shown that psychological violence alone can negatively impact CP severity and disability [166,167].

Regarding our second hypothesis, we expect that aggressors will present more hostility and criticism toward their partners’ health conditions as a way to undermine them, increase dependence, and control them, considering violence as an instrumental component [165]. We also expect that periods of violence will be linked to an increase in CP symptomatology. However, in women with CP alone, their partners will likely promote autonomy by encouraging and reinforcing healthy behaviors or promote dependence by maintaining disabling pain behaviors through solicitousness. In this group of women, even if hostile responses can also be present sometimes, their impact on CP will be less significant because they need to take place in a context of low marital satisfaction [95,96], and we assume that levels of marital satisfaction will be higher among women with CP alone. In addition, we expect that periods with an increase in CP symptomology will be more related to external stressors than to the relationship itself.

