Second, we aim to identify whether women with CP alone, those with CP and currently experiencing IPV, and those with CP and a past history of IPV present different profiles based on risk and protective factors for (disabling) CP and health outcomes. We hypothesize that women with CP and current or past experiences of IPV will show higher levels of disabling pain, more excessive persistence or avoidance activity patterns, lower levels of exercise, worse pain-related self-efficacy, greater pain worrying, informal social support that fosters dependence, lower levels of physical functioning, greater anxiety and depression, poorer medication management, increased illegal drug use, more suicidal thoughts and attempts, and a higher frequency of health system use. This hypothesis is based on previous findings indicating higher levels of disabling pain in women experiencing IPV compared to those with CP alone, as well as higher levels of suicidal thoughts, addiction issues, and greater use of health services compared to the general female population [23,165]. These characteristics will likely worsen in the presence of PTSD [82]. In addition, because pain-related self-efficacy and pain worrying have been linked to CP [65-69,78], we expect these factors to most effectively account for the profiles of women with a current or past history of IPV, along with informal social support, for the aforementioned reasons.

Moreover, because AI techniques go beyond traditional inferential statistics, it can identify patterns and relationships between variables that might remain undetected by the human eye. AI may uncover specific profiles within different groups of women, revealing how factors such as educational background, traditional feminine roles, ethnicity, and the duration of violence intersect with CP-related variables; for example, it could be that the pattern of excessive persistence is more common in women who are in the initial stages of the relationship and that they may seek to conform to traditional gender roles in an effort to meet their aggressors’ expectations. AI’s ability to process large datasets could lead to new insights and advances in understanding pain, its management, and its relationship with other concurrent psychosocial factors.

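### The only health-service-use item has overlapping and partly non-frequency answer options and covers GP visits alone, so the hypothesis on health system use can be assessed only crudely and only for GP care

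*Protocol article*

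**What the plan says.** The section Health Service Use: Ad Hoc Questionnaire is the only description of this measure, and Table 2 lists no other instrument for it. The stem is a frequency question: "they will be asked how many times per month they visit their general practitioner". The answers are fixed as "none, only when needing medication prescriptions or check-ups, at least once a month, or ≥2 times per month".

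The measure serves the second hypothesis in the Discussion (Summary), that women with current or past IPV will show "a higher frequency of health system use". The same section, giving the reasons for the first aim's hypotheses, expects IPV to lead to more medication use and "more frequent visits to health centers". The background section CP Outcomes says of people with chronic pain that "they are more likely to use emergency services and unscheduled care".

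The phase 2 Data Analysis section names t tests and "ANOVA to compare means across groups" without assigning a test to any variable. It also plans feature ranking and machine learning classifiers. The phase 1 Overview says that phase 1 may "incorporate any additional relevant factors or health outcomes" into phase 2, but it specifies nothing for service use.

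**The concern.** A frequency item needs categories that exclude one another, cover every case and share one scale. This item falls short on all three, and the article gives the options in full, so the fault does not come from condensation.

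The effect is misclassification of visit frequency, and it need not be equal across groups. The protocol expects women exposed to IPV to use more medication. A woman who attends often, but for prescriptions, can truthfully choose the option that records no frequency. If that happens more in the IPV groups, frequent visitors there drop out of the high-frequency options, and the predicted difference shrinks or disappears.

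The second issue is scope. The hypothesis concerns the health system, while the item concerns one service. A shift from GP care to emergency care would appear as lower use.

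**Working it through.** **1. Reading the options against the stem**

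| True behaviour | Options that are truthfully available |
|---|---|
| Never visits | first |
| Every two or three months, for pain | none fits clearly; the first is nearest, as zero in a typical month |
| Once a month, only for prescriptions | second or third |
| Once a month, for pain | third |
| Three times a month, for pain | third or fourth |
| Three times a month, only for prescriptions | second, third or fourth |

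The first, third and fourth options can be ranked, although the fourth is nested in the third. The second has no fixed rank. Merging the third and fourth resolves the fifth row. It does not resolve the third and sixth rows, where the second option still competes.

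**2. Scope.** Set side by side, the hypothesis speaks of health system use, the background names GP, emergency and unscheduled care, and the item asks about the GP only.

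**3. The plan's own figure.** The only sample size is 359, calculated for pain avoidance and not for this item. It is reproduced here only because its group sizes are used in step 4.

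- Inputs (Sample Size Calculation): "the expected prevalence ratio assumed to be 2.0", 20% prevalence (read as the unexposed prevalence, so 40% in the exposed), 30% exposed (k = 70/30), alpha 5% (two-sided assumed), power 90%.
- Formula: n = [z(0.975)·√((1+1/k)·p̄(1−p̄)) + z(0.90)·√(p1(1−p1) + p2(1−p2)/k)]² / (p1−p2)², with p̄ = 0.3×0.40 + 0.7×0.20 = 0.26. This gives 75.64.
- Continuity correction: n/4 · [1 + √(1 + 2(k+1)/(n·k·(p1−p2)))]² = 82.63, rounded up to 83 exposed.
- Unexposed: 82.63 × 70/30 = 192.80, rounded up to 193.
- Adding a second exposed group of 83 gives 83 + 83 + 193 = 359, as stated.

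**4. Illustration of size.** The documents give neither GP-visit rates nor misclassification rates, so all percentages below are assumptions. The comparison is one IPV group (83) with chronic pain alone (193), two-sided 5%.

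Power = Φ{[|p1−p2| − 1.96·√(p̄(1−p̄)(1/83+1/193))] / √(p1(1−p1)/83 + p2(1−p2)/193)}, where p̄ is the pooled proportion.

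For 40% versus 20%: p̄ = (33.2 + 38.6)/276 = 0.260, and (0.20 − 1.96×0.0576)/0.0610 = 1.43, so power is 92%.

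*Effect of the overlap* (true share with two or more visits a month: 40% IPV, 20% chronic pain alone)

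| Share of these women ticking the third option | Observed | Power |
|---|---|---|
| 0% in both groups | 40% v 20% | 92% |
| 25% in both | 30% v 15% | 80% |
| 50% in both | 20% v 10% | 61% |
| 50% in IPV, 0% in the other | 20% v 20% | difference vanishes |
| 0% in IPV, 50% in the other | 40% v 10% | difference inflated |

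*Effect of the reason-based option after merging the top two* (true share visiting at least monthly: 60% IPV, 40% chronic pain alone)

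| Share of these women ticking the second option | Observed | Power |
|---|---|---|
| 0% in both groups | 60% v 40% | 87% |
| 25% in both | 45% v 30% | 67% |
| 50% in both | 30% v 20% | 44% |
| 50% in IPV, 25% in the other | 30% v 30% | difference vanishes |

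**The case against.** Several points on the other side are sound.

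- **A test remains possible.** A reader might infer that the hypothesis cannot be tested, or that the data are beyond repair once collected. The documents do not support that. The top two options can be merged into at least monthly versus the rest, or the four options compared as nominal categories. Either gives a GP comparison, with the reason-based option still blurring it.
- **The options are not wholly unordered.** Only the second lacks a rank. Many women with two or more visits may also choose the more specific option when they see both.
- **ANOVA is not assigned to this item.** The Data Analysis section names it in general terms, and the choice of test per variable is commonly left to an analysis plan that is not shown. It would be unfair to say that a mean of these codes is planned.
- **This is not a headline outcome.** The abstract gives health care use as one example, the hypothesis lists it last among about a dozen differences, and the sample size does not rest on it.
- **GP visits are a defensible, low-burden proxy.** The background also stresses primary care, and questionnaire length is an acknowledged limitation. Adding emergency care items is a preference. The mismatch between hypothesis and measure is real, but narrower wording would also settle it.

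None of this answers the nested categories, the option that is a reason, or the missing place for less-than-monthly visits. The power losses rest on assumed rates. They show how the error would act, not how large it will be.

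**Conclusion.** The concern holds in this limited form. As written, the item will misclassify visit frequency, possibly to different degrees across the groups, and later merging cures only part of it. The hypothesis on health system use can be assessed only for GP care, and only crudely.

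The faults in the options follow from reading them and need no assumption. The size is unknown. Under the assumed rates, equal misclassification of 25% to 50% lowers power from 92% to between 80% and 61%, or from 87% to between 67% and 44% after merging. Unequal misclassification can remove or inflate the difference. The effect is confined to one of many secondary outcomes. The sample size and the other outcomes are untouched. It is worth correcting because the edit is small, and because phase 2 responses are anonymous to the research team, so true counts are unlikely to be recoverable later.

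**What to change.** Before phase 2 data collection:

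1. Replace the options with exclusive and exhaustive frequencies, for example: none; less than once a month; once a month; two or more times a month. A count over a fixed recall period would serve equally well.
2. Ask separately whether visits are only for prescriptions or check-ups.
3. Analyse the answer as an ordinal variable, or as a count if counts are collected.
4. Either limit the hypothesis in the Discussion to GP visits, or add short items on emergency and unscheduled care.

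The cost is one or two extra short items in an already long questionnaire and a re-check of the piloted form. The timeline in Table 3 already allows for piloting and changes before phase 2 collection. If collection has started, the fallback is to merge the top two options, report the prescriptions or check-ups option as its own category, and state the limitation.
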